### Objectives

The objectives of the trial are:To evaluate whether allocation to municipal budget and debt counselling services via the HWF model and provision of a financial guidance book (intervention arm) has an effect on self-reported child deprivation in comparison to similar families who only receive the financial guidance book (waitlist-control arm).To evaluate whether allocation to the intervention arm has an effect on self-reported financial knowledge, financial control, readiness for change, attainment of personal goals to improve one’s financial situation, parental mental health and financial stigma, which relate to the model theory of change.To describe the amount of financial gain, and sources of income, that can be attributed to the HWF model.To assess whether effects on self-reported child deprivation, financial control, financial knowledge, readiness for change, personal goals, parental mental health and financial stigma are maintained 12 months post-randomisation.To estimate the cost-effectiveness of the HWF model.

It is hypothesised that, when compared with the waitlist-control arm 3 months post-randomisation, families in the intervention arm will report a lower rate of child deprivation, measured as necessary items lacking on a standardised list, due to inability to cover costs. It is further hypothesised that, when compared with the waitlist-control arm, the intervention arm will report greater financial control and knowledge, and lower levels of mental health difficulties and financial stigma.

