## Method

### Design

A two-arm randomised waitlist-control superiority trial (1:1 allocation ratio) will be conducted to evaluate the effectiveness of the HWF model in improving the financial situation of families who have self-reported economic difficulties. The intervention arm will be referred to budget and debt counselling immediately after randomisation and the waitlist-control arm 3 months later. Informed by Patient and Public Involvement (PPI), so all participants receive some form of support at randomisation, both arms will be offered a freely available financial guidance book. RCT assessments will take place at two points: pre-intervention (T1) and post-intervention (T2; 3 months after randomisation).

A longitudinal cohort study will be conducted with all participants, from both trial arms (intervention and waitlist-control). Longitudinal assessment will take place 12 months after randomisation (T3), to assess any changes in measures between T2 and T3. See Fig. 2 for the participant timeline.

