### Control arm

As described above, all participants receive a copy of the book. Those randomised to the waitlist control arm will be referred to the local financial counselling service after a period of 3 months.

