### Statistical methods

Baseline and demographic characteristics will be summarised using means and standard deviations (or medians and interquartile ranges) for continuous variables and percentages for categorical variables. For items that align with national survey questions, population-level comparisons will be made. Descriptive data will also be reported on process outcomes, e.g. number of families screened, proportion eligible for inclusion, and proportion consenting to participate.

The primary comparison of the trial arms will use an intention-to-treat framework. A regression analysis will be undertaken to quantify the extent to which a potential intervention effect on the primary outcome is determined by allocation to the intervention. Per-protocol comparison will be performed as a secondary analysis. Further moderation analyses will examine the associations between outcomes and participants’ characteristics. Differences in the means and proportions on measures between T2 and T3 will be assessed using parametric and non-parametric tests.

The cost-effectiveness analysis will compare the two arms of the trial at T2 follow-up using capability-adjusted life-years (CALY) gained as the outcome of interest. To analyse the cost differences between the two arms, we will collect information about intervention costs (i.e. personnel time, material, etc.) and societal resource use. We will express the final output as a cost/ CALY. Results will be presented as incremental cost-effectiveness ratios (ICER, expressing the cost per additional CALY gained). Uncertainty will be demonstrated using a cost-effectiveness acceptability curve, using bootstrapped regression estimates [5].

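### The 12-month maintenance question is analysed as a T2–T3 change in a cohort of both arms with no stated split by arm, although the waitlist arm is referred to counselling at about T2

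*Protocol article*

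**What the plan says.** All references are to the protocol article.

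- **Question.** Under Objectives, the fourth aim is to assess whether effects on child deprivation and the secondary measures "are maintained 12 months post-randomisation".
- **Population.** Under Design: "A longitudinal cohort study will be conducted with all participants, from both trial arms (intervention and waitlist-control").
- **Contrast.** Also under Design: "Longitudinal assessment will take place 12 months after randomisation (T3), to assess any changes in measures between T2 and T3".
- **Test.** Under Statistical methods: "Differences in the means and proportions on measures between T2 and T3 will be assessed using parametric and non-parametric tests". The article gives no arm term, within-arm analysis or criterion for maintenance.
- **Timing of counselling.** Under Design: "The intervention arm will be referred to budget and debt counselling immediately after randomisation and the waitlist-control arm 3 months later". The Control arm section repeats that waitlist families "will be referred to the local financial counselling service after a period of 3 months". T2 is labelled "post-intervention (T2; 3 months after randomisation") for the trial as a whole.
- **Stated limit.** The strengths and limitations list presents the 12-month assessment as exploration of longer-term effects and says that groups cannot be compared at that stage.

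**The concern.** T2 means different things in the two arms. In the intervention arm it follows referral to counselling, so T2–T3 change speaks to whether any benefit lasts. In the waitlist arm it falls at about the time of referral, so T2–T3 change describes what happens once counselling starts. A single T2–T3 difference over everyone averages the two and estimates neither.

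The trial's own hypothesis is that counselling lowers deprivation, so improvement in the waitlist arm after T2 is what the investigators should expect. That improvement would offset relapse in the intervention arm, or make simple persistence look like further improvement. The stated limit on group comparisons at 12 months does not cover this, because it concerns comparing the arms and not mixing them. At stake is the answer to one of five objectives, for which the article plans a separate publication.

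**Working it through.** **Plan's own figures.** The article gives no figure for the T2–T3 analysis. The inputs borrowed here come from Sample size: a 1-item difference, SD 3, and 142 families (71 per group). That sample size does not reproduce as a two-sided, two-group calculation: 2 × (1.96 + 0.84)² × 3² / 1² ≈ 142 per group. This is a separate matter, and nothing below depends on it; 71 is used only as the planned arm size.

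**Assumptions not in the article.** The T2–T3 correlation r is taken as 0.3 to 0.7. Losses and gains of 0 to 1 item are considered, with equal arms at T3. The projected 50% loss to follow-up is not tied to a time point in the text, so full and halved numbers are both shown.

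**Combined change.** The outcome is the number of items lacked, so a negative change is improvement. Let L be the rise in the intervention arm from T2 to T3 (effect lost) and g the fall in the waitlist arm (gain after counselling starts). With 1:1 arms:

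combined mean change = (L − g) / 2

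The within-arm SD of change is 3 × √(2(1 − r)). The SD of change across the combined cohort is √(within-arm SD² + ((L + g)/2)²). Chances below are for a two-sided 5% test of the combined change with N = 142, at r = 0.3 / 0.5 / 0.7.

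| L | g | Combined change | Result of the combined test |
|---|---|---|---|
| 0 (fully maintained) | 1 | (0 − 1)/2 = −0.5 | significant improvement in 38% / 50% / 71% |
| 0.5 (half lost) | 1 | (0.5 − 1)/2 = −0.25 | significant improvement in 13% / 16% / 23% |
| 1 (fully lost) | 1 | (1 − 1)/2 = 0 | about 2.5% significant in each direction |
| 1 (fully lost) | 0 | (1 − 0)/2 = +0.5 | significant worsening in 38% / 50% / 71% |

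Check of the first row at r = 0.5: SD = √(9 + 0.25) = 3.04, SE = 3.04/√142 = 0.255, and 0.5/0.255 = 1.96, hence 50%. With 71 families in total, the first row becomes 22% / 28% / 43%.

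The sign reverses only when waitlist families gain more than intervention families lose (second row). If waitlist families gain nothing, the sign is right but the estimate is half the true loss (fourth row).

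**Intervention arm alone.** The mean change estimates L directly. The 95% half-width is 1.96 × 3 × √(2(1 − r)) / √n:

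- n = 71, r = 0.5: 1.96 × 3 / √71 = 0.70 items (0.83 at r = 0.3, 0.54 at r = 0.7).
- n = 35.5 (half remain), r = 0.5: 1.96 × 3 / √35.5 = 0.99 items (1.17 at r = 0.3, 0.76 at r = 0.7).

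Full relapse (L = 1) would show as a significant worsening in 66% / 80% / 95% of trials with 71 families, and in 39% / 51% / 73% with half of them.

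**The case against.** **Pooling is inferred.** A reader might conclude that the protocol commits to a pooled test. It does not say so. Design states who is followed, and Statistical methods states the contrast and the test; neither says that the arms are combined. Allocation is known to the analysts (Blinding) and attendance is recorded (Intervention fidelity), so a by-arm analysis is possible. A full protocol or SAP may specify one, and the mixing problem would then disappear. This stands, and it is why the point is conditional on reading the article as written. Even so, one cohort of everyone, one T2–T3 contrast, no arm term and no group comparison at 12 months most naturally describe a single combined change.

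**The decision rule is inferred too.** A reader might suppose that a non-significant T2–T3 difference will be reported as maintenance. No section says that. The caution against such a reading is worth writing down, but the article cannot be charged with having adopted it.

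**The follow-up is labelled exploratory.** This stands and lowers the weight of the point. The disclosed limit does not, however, mention that the two arms start counselling at different times relative to T2.

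**The alternative is also limited.** An intervention-arm change has no untreated comparator after T2, so any general trend is mixed with loss or persistence of effect. Adding T1–T3 change would not cure this and would bring in regression to the mean, because families enter by screening positive for hardship. This stands as well: a by-arm analysis is better evidence on objective 4 but does not settle it.

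**Conclusion.** The point holds in a limited form. Followed as written, the T2–T3 analysis estimates (L − g)/2, which is not the quantity objective 4 asks about. With an assumed 1-item gain in waitlist families, full relapse in the intervention arm gives 0 and perfect maintenance gives −0.5 items. These are illustrations: the 1-item figure is borrowed from the sample-size section, and neither relapse nor waitlist gain is predicted in size by the article.

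A reader might infer that the whole longitudinal study is bound to give a wrong answer, or that the trial cannot proceed without this change. The article does not support that. The primary comparison at T2 and the cost-effectiveness comparison at T2 are untouched. The affected objective is secondary and exploratory, and the data needed for a better analysis are already planned. This is a cheap improvement, not a must-fix.

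**What to change.** State in Statistical methods that T2–T3 change is estimated separately by arm, for example from one mixed model with an arm-by-time term. Then:

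- Present the intervention-arm change with its 95% CI as the evidence on maintenance.
- Report the waitlist-arm change separately, as an uncontrolled pre-post estimate around the start of counselling.
- Describe both as uncontrolled after T2.
- Say that maintenance will not be concluded from a non-significant difference alone. A margin set in advance would sharpen this, but it is a matter of choice and could sit in the SAP.

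If a full protocol or SAP already analyses T2–T3 change by arm, one sentence saying so is enough.

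The cost is wording plus precision; no new data are needed. The maintenance estimate rests on about half the cohort, and if half of the intervention families are lost its interval of roughly ±1 item is as wide in each direction as the 1-item difference the trial was sized on.

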## Strengths and limitations of this study

• This study will assess the effectiveness of the Healthier Wealthier Families (HWF) model on self-reported child deprivation in Sweden by randomised controlled trial• The study design includes measures on a number of hypothesised mediators, namely self-reported financial knowledge, financial control, readiness for change, parental mental health and financial stigma, which will give insight to the intervention logic model• Data on income, and sources of income, will allow the amount of financial gain that can be attributed to the HWF model to be described• Inclusion of personal goal attainment as an outcome will allow participants to express intervention expectations in their own words and report on how far these expectations have been met• The study design includes a cost-effectives evaluation that will consider group differences in capability-adjusted life-years• An internal pilot will assess the feasibility of the RCT processes• A 12-month follow-up will allow for exploration of whether any effects are maintained in the longer-term, albeit without the ability to make group comparisons at that stage

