### Sample size

The primary analysis for the RCT will be a comparison of the unweighted mean number of child material and social deprivation (MSD) items lacked (T2). The target sample size has been calculated based on this primary analysis. The power calculation has been informed by child MSD data for Sweden collected via the European Union Statistics on Income and Living Conditions (EU-SILC) survey, which reports an unweighted mean of 4.5 items lacked among the materially-deprived population. Using a significance level of 0.05 and 80% power, a total of 142 families (71 per group) will be required to detect a 1-item group difference in the unweighted mean number of child MSD items lacked, assuming a standard deviation of 3. As the trial will be conducted in areas with high rates of socioeconomic disadvantage, we estimate that up to 30% of families will experience financial hardship and be eligible for inclusion. The estimated rate of uptake is 50% among eligible families, based on a pilot in the Sandviken municipality, Sweden. Loss to follow-up is projected at 50%. See Fig. 2 for the participant timeline with projected numbers.

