### Measures

The primary outcome measure for the RCT is child material and social deprivation (MSD). Secondary measures include household income and sources of income, financial knowledge, financial control, readiness to change, personal goal attainment, parental mental health, and financial stigma. These measures will be administered at all time points and assessed at T2 (for the RCT) and T3 (for the longitudinal cohort study). See Fig. 3 for an overview of the enrolment, intervention and assessment schedule.

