### Data collection

T1 data collection and randomisation is planned to take place between September 2022 and June 2024. T2 data collection occurs around 3 months after T1 data collection, and is therefore due to take place between December 2022 and September 2024. T3 data collection occurs 12 months after T1 data collection and is due to take place between September 2023 and June 2025.

Data will primarily be collected using REDCap. The study questionnaire can be completed via an electronic link. Alternatively, it can be completed over the phone with a member of the research team, or on paper via post. This inclusive data collection practice allows for participant preferences to be taken into account and overcomes potential literacy difficulties that could be present in the target population. The screening form includes a question on need for interpretation, which will be consulted prior to the research team contacting the parent/caregiver to allow for necessary interpreter arrangements to be made. Participants will be offered shopping vouchers at T2 and T3 to compensate for their time completing the study questionnaire. Data will be exported into the Statistical Package for the Social Sciences (SPSS) for analysis. Participant identity numbers will be used. The file will be saved on the university server, which is automatically backed up. All data management procedures comply with current regulations on personal data management.

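### For the 12-month question the plan names only two-occasion tests of the T2–T3 difference, and with selective loss to follow-up such tests can show a change that did not occur

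*Protocol article*

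**What the plan says.** The Design section sets up the follow-up: "A longitudinal cohort study will be conducted with all participants, from both trial arms (intervention and waitlist-control"). Its purpose is given there too: "Longitudinal assessment will take place 12 months after randomisation (T3), to assess any changes in measures between T2 and T3". It serves the fourth objective, which asks whether effects "are maintained 12 months post-randomisation". The waitlist arm is referred to counselling after 3 months, so the strengths and limitations list describes the 12-month follow-up as exploratory, "albeit without the ability to make group comparisons at that stage".

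The only analysis named for this is in Statistical methods: "Differences in the means and proportions on measures between T2 and T3 will be assessed using parametric and non-parametric tests". Pairing, analysis set and the handling of families without T3 are not stated. The intention-to-treat framework in the same section is stated for the comparison of arms.

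On the data available, the Measures section says: "These measures will be administered at all time points and assessed at T2 (for the RCT) and T3 (for the longitudinal cohort study"). Randomisation follows T1 collection, so every randomised family should have a T1 score on the primary outcome. On attrition, the Sample size section says "Loss to follow-up is projected at 50" per cent, without saying by which visit.

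**The concern.** A test of two occasions has two simple forms, and each handles partly followed families badly unless missing values are imputed. The paired form keeps only families seen at both T2 and T3. If families with high T2 scores tend not to return, those who do return had T2 scores that were low partly by chance, and their drift back towards the mean is read as worsening. The unpaired form sets all T2 responders against whoever remains at T3, so the changed mix of families is read as improvement, and the correlation within families is ignored. Neither form draws on T1.

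At T3 there is no control comparison against which such an error would show. At stake is the answer on maintenance: an effect could seem to fade or to grow because of who stayed in the study.

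**Working it through.** The article gives no figure for the T2–T3 analysis, so there is none to reproduce.

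**Inputs from the article (Sample size):** SD 3 items; 1-item target difference; 50% loss, no time point.

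**Assumptions:** no true change; normal scores with equal SD at each visit (the outcome is really a 0–17 count); a common correlation ρ = 0.5 between visits, range 0.3–0.7; T3 return a = 80% for families at or below the mean of the score that drives loss, b = 50% above it; 142 families seen at T2. The 142 is the number the article calls required. It affects the rejection rates, not the biases.

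**Step 1. Shift among returners in the score that drives loss.** Half of a standard normal distribution has mean ±0.798, so the shift is −0.798 × SD × (a − b)/(a + b):
- 80%/50%: −0.798 × 3 × 0.30/1.30 = −0.552
- 90%/40%: −0.798 × 3 × 0.50/1.30 = −0.921

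**Step 2. Loss driven by the T2 score.** Returners' T2 mean shifts by −0.552 and their T3 mean by ρ × (−0.552).
- Paired error: (1 − ρ) × 0.552 = +0.387, +0.276, +0.166 for ρ = 0.3, 0.5, 0.7
- Unpaired error: −ρ × 0.552 = −0.166, −0.276, −0.387

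If the less deprived families are the ones lost, both signs reverse.

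**Step 3. False rejection by the paired 5% test, ρ = 0.5.** Pairs: 142 × 0.65 = 92. Standard error: 3 × √(2 × 0.5)/√92 = 0.313.
- 80%/50%: 0.276/0.313 = 0.88, about 14% rejection
- 90%/40%: error 0.5 × 0.921 = 0.460; 0.460/0.313 = 1.47, about 31%

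**Step 4. Other loss mechanisms, 80%/50%, ρ = 0.5.** The model column predicts T3 from T1 and T2, each with slope ρ/(1 + ρ) = 1/3, and averages over all families. It stands in for a likelihood-based repeated-measures model.

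| Loss driven by | Shift T1 / T2 / T3 | Paired | Unpaired | Model |
|---|---|---|---|---|
| T2 | −0.276 / −0.552 / −0.276 | +0.276 | −0.276 | −0.276 + (0.276 + 0.552)/3 = 0 |
| T1 | −0.552 / −0.276 / −0.276 | 0 | −0.276 | −0.276 + (0.552 + 0.276)/3 = 0 |
| Average of T2 and T3 | −0.319 / −0.478 / −0.478 | 0 | −0.478 | −0.478 + (0.319 + 0.478)/3 = −0.212 |
| T3 | −0.276 / −0.276 / −0.552 | −0.276 | −0.552 | −0.552 + (0.276 + 0.276)/3 = −0.368 |

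In the third row the average has SD 3 × √0.75 = 2.598, so it shifts by −0.798 × 2.598 × 0.30/1.30 = −0.478, and T1 shifts by (0.5/0.75) × (−0.478) = −0.319.

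Simulation of these settings (8,000 trials each) agreed with the table to within 0.01 items. With loss driven by T2, the paired test rejected in 10% to 17% of trials over ρ = 0.7 to 0.3.

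**Step 5. A different loss model.** Logistic loss on T2 with odds ratio 2 per SD, ρ = 0.6 and 142 families at T2 gave:
- 20% loss: paired +0.15 (9% rejection), unpaired −0.23
- 30% loss: paired +0.23 (13%), unpaired −0.34
- 50% loss: paired +0.37 (22%), unpaired −0.56

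With 71 families at T2 and 30% loss the biases were about the same and paired rejection was 9%.

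**The case against.** Four points can be made for the plan.

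1. **The article condenses.** Pairing, analysis set and missing-data handling are commonly left to a full protocol or analysis plan, which is not shown. This stands: their absence is not an error, and a reader should not infer that the plan has settled on a complete-case test. What remains is that the article does name a method. A model using all three visits would replace that method, not fill it in.

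2. **The 50% loss is not a T2–T3 figure.** This stands. A reader might take it as the loss between those visits, but the text does not say so. The return rates above are assumptions.

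3. **The follow-up is exploratory and attrition is not ignored.** Vouchers, several modes of completion and attrition analyses on demographic data are planned. This limits the importance of the point. However, nothing links the attrition analyses to the T2–T3 estimate.

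4. **The proposed model is not always better.** This stands too. When loss follows the T2/T3 average, the paired test is unbiased and the model is off by about −0.21. When loss follows T3, both are biased and the model more so (−0.37 against −0.28). The documents do not show which mechanism will apply, so the paired test should not be discarded.

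**Conclusion.** The point holds as a weakness in the method named for the 12-month question. The two-occasion tests leave collected data unused and, without imputation, can turn selective loss into apparent change. If loss depends on the T2 score, the error is about +0.28 items paired and −0.28 unpaired under 80%/50% return, SD 3 and correlation 0.5. Under 90%/40% return the paired error is 0.46, nearly half the 1-item target. In each selective-loss mechanism tabulated, at least one of the two forms is biased, and the article does not say which form will be used.

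A reader might infer that selective loss always gives errors of opposite sign. That is so only when loss follows the T2 score. When loss follows T1 (with equal correlations) or the T2/T3 average, the paired test is essentially unbiased. When it follows T3, both tests err in the same direction. The sizes rest on assumed return rates, correlations and normality. The primary comparison at T2 is not affected.

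**What to change.** Replace the sentence in Statistical methods with text such as:

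*Scores at T1, T2 and T3 will be analysed together in a likelihood-based linear mixed model for repeated measures (a logistic mixed model for the 3-item deprivation threshold) with arm, time and arm-by-time terms. All randomised families with any observation will be included, and the T2–T3 change will be estimated within arm. Personal goal attainment, rated only at T2 and T3, will be modelled with those two visits as outcomes. The paired comparison of families seen at both T2 and T3 will be reported alongside. A sensitivity analysis will examine loss that depends on unobserved T3 scores.*

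A mixed model is preferable here to generalised estimating equations for the threshold outcome, because those are not in general protected under missing-at-random loss.

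The cost is wording and a modest amount of analysis. No further families or data are needed, and mixed models run in the planned software: "Data will be exported into the Statistical Package for the Social Sciences (SPSS) for analysis". The downside is reliance on loss being missing at random given the observed scores and arm. If loss depends on unseen T3 values, the model can be more biased than the paired test, which is why both should be reported with the sensitivity analysis.
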